## Methods

### Design

The study will be conducted in a double-blind, placebo-controlled, parallel-group design with 20 study participants per group. This trial will take place at the Department of Psychiatry and Psychotherapy of the Ludwig-Maximilians-Universität Munich (LMU). Participants with a primary MDD diagnosis according to the Diagnostic and Statistical Manual of Mental Disorders, 5th Edition (DSM-5), will perform a 6-week self-administered treatment with prefrontal active tDCS or sham tDCS at home; either as a monotherapy or as an adjunctive treatment to stable antidepressant medication. Participants will be divided (1:1) into two groups by fixed-blocked randomization, each group receiving either active tDCS or sham tDCS for a total of 6 weeks (5x/week, maximum 30 sessions). At baseline, optional cranial MRI (cMRI), consisting of structural MRI (sMRI) and functional MRI (fMRI), will be performed. E-field modeling, based on the cMRI scans, may also take place. During the treatment phase, a study visit will take place every 2 weeks. An additional study visit will take place after the first week addressing any difficulties with self-application at home. After 6 weeks, the primary endpoint will be reached concluding the treatment phase. The final rating will be made in the ensuing follow-up phase, consisting of study visit 5 and 6 (V5) (V6). V5 and V6 will take place 4 weeks and 8 weeks, respectively, after the last stimulation session (Fig. 1). According to the *DepressionDC* trial [41], a total of 4 sessions may be missed without denoting a drop-out. Missed sessions can be compensated with additional sessions in week 7. All devices used in this study have CE certifications.

**Fig. 1 Fig1:**
[figure not shown]
Study design

### Study objectives

The present project aims to investigate the feasibility, effectiveness, and safety of bifrontal tDCS as an at home treatment approach to MDD in a placebo-controlled, parallel-group design. The study objectives regarding feasibility consist of demonstrating that a 6-week home-based stimulation is feasible for patients with MDD.

The primary outcome is feasibility based on successfully completed stimulations and drop-out rates. *HomeDC* considers the intervention to be feasible when 20 out of 30 sessions have been fully conducted by at least 75% of the participants. This definition of testing feasibility is the same as a recent trial protocol, the *DiSCoVeR* trial [31]. *DiSCoVeR* set its target to a minimum of 50%, due to its combination of tDCS and gamification applications. Using this framework, *HomeDC* chose a target between 50% and the ceiling value of over 90% reported in aforementioned trials [26, 30]. Secondary outcomes are safety, based on side effects and complications encountered, as well as stimulation discontinuation rates due to high impedances. Safety is measured based on the number of adverse events (AE) or serious adverse events (SAE) as well as adverse device effects (ADE) and serious adverse device effects (SADE). A comfort rating questionnaire (CRQ) will be completed by the study participants after each session as a safety measurement tool [42]. On a scale from 1 to 10, participants note perceived subjective intensity of brain stimulation relevant side effects. This self-report questionnaire allows the research team to detect and follow up on any AEs, as well as monitor tolerability. Effectiveness is measured by a reduction in the Montgomery and Asberg Depression Rating Scale *(*MADRS) after 6 weeks of at-home tDCS treatment. We will use MADRS scores to calculate response and remission rates in both groups. Response is defined as a reduction ≥ 50% in MADRS score and remission as MADRS score < 11 [43].

Further outcomes are the changes in the Beck Depression Inventory (BDI), the General Assessment of Functioning (GAF), and the Clinical Global Impression-Improvement/-Severity (CGI-I/-S) scores. In both active and sham tDCS groups, baseline measurements will be compared to measurements documented at the primary endpoint after 6 weeks and during the follow-up visits. Stored data on timing, impedance, voltage, and current flow will be transmitted to measure stimulation quality (Fig. 2).

**Fig. 2 Fig2:**
[figure not shown]
Technical workflow

### Participants

Potential study participants, presenting with MDD, are recruited from the brain stimulation outpatient clinic of the LMU and through local advertising (each approved by the ethics committee). Patients of the psychiatric day-care hospital of the LMU may be approached by recruitment members of the research team. State of research, background, and possible benefits and risks of tDCS, as well as the design of the study are thoroughly explained. Potential participants are specifically informed that they may receive sham tDCS and that an improvement of their MDD symptoms cannot be guaranteed. Potential participants may take as much time as they need to decide whether they are willing and able to take part in the study. To this effect, they will be given the contact information of a member of the research team in case they have any more questions and/or decide to participate. After reaching out, all potential participants are given an appointment for eligibility screening. Study participants receive a cost reimbursement of 55 euros for travel expenses. All study participants have complete insurance for study procedures and travel to the study center through ECCLESIA mildenberger HOSPITAL GmbH.

#### Eligibility criteria

Males and females between 18 and 70 years of agePrimary diagnosis of unipolar Major Depressive Episode (single or recurrent) according to DSM-5 criteria as assessed by the Mini International Neuropsychiatric Interview (M.I.N.I) [44]Current episode present for at least 4 weeks, but lasting no longer than 5 years, at the time of study inclusion (in between episodes there must be a period of ≥ 2 months, in which the participant did not meet full criteria for the DSM-5 definition of major depressive episode).Total score ≥ 13 in the Hamilton Depression Rating Scale (HDRS-17) [45] during screeningNo medication or stable medication for at least 2 weeks at time of screening. Allowed medications are (also in combination): selective serotonin reuptake inhibitors (SSRIs), selective serotonin–norepinephrine reuptake inhibitors (SSNRIs), serotonin–norepinephrine–dopamine reuptake inhibitors (SNDRIs), Mirtazapine, Vortioxetine, Agomelatine, Trazodone, Tianeptine, Opipramol, Moclobemide, and tricyclic antidepressants.

In addition, a stable dosage of an augmentative combination (antidepressant base drug) for at least 2 weeks is also allowed as follows: Quetiapine, Aripiprazole, Risperidone, and Olanzapine.

Other antipsychotics may also be combined if the dose is stable for at least 2 weeks prior to the start of treatment. They must not reach the threshold of the minimally effective dose according to the antidepressant treatment history form (ATHF). Combination with lithium is allowed if lithium dosage is stable for at least 3 months prior to study inclusion.

Rescue medication with Zopiclone (on demand up to 7.5 mg/day orally), Zolpidem (up to 10 mg/day), and Benzodiazepine up to a dose equivalent to 2 mg of Lorazepam is allowed.

All medication taken by a study participant during treatment and/or taken up to at least 4 weeks before treatment start must be documented. During the course of the trial (treatment and follow-up phase), the medication dose should not be changed.Concomitant psychotherapy is permitted. Type, modality (e.g., group vs. individual therapy), duration, and frequency of therapy must be accurately documented.Participant is capable and willing to provide informed consent.*Exclusion criteria*Acute risk for suicide, defined as a score of 4–10 on item 10 of the MADRS [46], or attempted suicide in the current episodeAny relevant psychiatric axis-I- and/or axis-II-disorders other than MDD assessed by M.I.N.I. to be the primary diagnosis. Depression as a secondary disease to another disease: e.g., psychotic disorder (current), bipolar disorder (lifetime), eating disorder, obsessive–compulsive disorder, post-traumatic stress disorder, generalized anxiety disorder, panic disorder, social phobia, personality disorder, and substance dependence in the past 6 months (nicotine and caffeine excluded).Any relevant neurological disorder including increased intracranial pressure, space-occupying brain lesions, history of cerebrovascular accidents, transient ischemic attacks within the last 2 years, cerebral aneurysm, dementia, Parkinson’s disease, Huntington’s chorea, multiple sclerosis, and epilepsy (including history of seizures).ECT in the current episodeHistory of tDCS, except for single tDCS sessions during experimental studiesIntracranial implants or any other intracranial metal objects (excluding the mouth) that cannot be safely removedConfirmed pregnancy (according to pregnancy test at baseline visit)Treatment with deep brain stimulation or vagus nerve stimulationAny relevant unstable medical conditionSite personnel and investigators, directly affiliated with this study

### Power analysis and sample size calculation

Considerations of adequate sample size for feasibility outcomes draw on previous study results, with sample sizes varying from case series [27, 45] to larger randomized controlled trials with up to 64 participants [28, 47]. The dropout rate or rate of missed stimulations also varies depending on the study protocol. A similar study protocol with only 4 weeks of stimulation plus taper phase (32 stimulations in total) was used by Alonzo and colleagues [26]. This study, albeit without sham control, involved 34 participants and resulted in a drop-out rate of 6% with 93% of sessions completed. Similar numbers were found in the trial of Woodham and colleagues. Of 26 participants included, 92.3% completed the 6-week treatment phase [30]. Thus, with respect to feasibility, a comparable sample was intended.

Regarding the antidepressant effects, a power calculation was performed based on the amputated intention-to-treat (ITT) sample of the SELECT trial [7]. The data set from this trial was available to our group for sample size calculation. The change in MADRS score between the placebo-medication/sham tDCS condition and the sertraline (50 mg)/active tDCS condition was used. A change in the MADRS score was hypothesized because the effects of tDCS are thought to be synergistic with existing serotonergic medication [48]. In this pilot study, participants should have been on stable medication for at least 2 weeks or be medication-free. Thus, at baseline, they had not yet responded adequately to existing medication as seen in a minimum HDRS-17 score of 13. Only active tDCS is expected to have a synergistic effect [49]. Since the 50 mg sertraline was a very low dose, the synergistic effect in the SELECT study [7] is questionable, but it can be assumed that study participants with stable serotonergic medication get such an effect, so that with the assumption of the effects of the two groups the achieved effect is not overestimated.

The difference of change in MADRS scores (pre-post treatment phase) between the two groups was *M* = 12.58 points. The standard deviation of the change was SD = 11.01 points. After week 6, this leads to a Cohen’s *d* of 1.14. With power = 0.90 and a two-sided test, the G*Power analysis results in a required participant number of 18 per group.

Assuming a significance level of *α* = 0.05 and power = 0.90, a total sample size of 36 study participants would detect a true group difference of 12.58 MADRS points. Further taking a drop-out rate of approximately 10% into account leads to a total recruitment number of 40 study participants.

### Interventions and procedures

TDCS will be performed according to the protocol of the *DepressionDC* trial [41] with the total number of stimulations increased to 30 sessions in order to achieve longer lasting effects. With more than 3200 completed stimulations, the protocol has proven itself credible in application and implementation. Participants will self-apply 5 tDCS sessions per week (Monday to Friday) for 6 weeks at home. Electrode montage will be bifrontal with the anode over F3 and the cathode over F4 (international 10–20 electroencephalogram system). Electric stimulation will be held at 2 mA in the active tDCS group. Each stimulation will last 30 min, with electric current ramp-in (15 s) and ramp-out (30 s) phases beginning and ending each session. The sham group will have ramp-in and ramp-out phases analogous to the active tDCS group. In contrast to the active group, the electric current will be turned off in between these phases during the 30-min sham stimulation period. To make positioning the electrodes at home easier and to avoid errors, a special stimulation cap will be used. This innovative cap, made by neuroConn (neuroCare Group, Illmenau, Germany), utilizes built-in electrodes over the corresponding target areas [50].

Five different manufactured cap sizes ensure correct electrode positioning for all head shapes (Fig. 3). At the screening visit, the head circumference as well as the distance between vertex and external eye angle will be measured (head position in the “Frankfurter Horizontale”; participant looks straight ahead into the distance). The appropriate cap is selected to match the participant’s individual anatomy. Using a syringe, a maximum of 20 ml of NaCl will then be injected into the opening provided for each electrode.

**Fig. 3 Fig3:**
[figure not shown]
Measurement of head circumference and distance between eye angle and vertex (1). Five cap sizes for different head shapes

*HomeDC* will use the same CE-certified stimulators from neuroConn as the *DepressionDC* trial. The stimulators and software were designed specifically for *DepressionDC* to ensure double-blinding (investigator and participant). Impedance, voltage, and current will be measured per second. This technical data will be recorded, stored, and transferred analogous to the *DepressionDC* trial [37]. For safety, an impedance control lock prevents stimulation at electrode impedances > 55 kOhm in accordance with the *DepressionDC* study. In addition, a pre-programmed safety mechanism only allows stimulation once a day. Stimulation is automatically locked for 16 h between sessions. After each treatment, participants also complete a CRQ to record potential side effects or AEs. These CRQS are monitored by the research team, in case they warrant further investigation and/or suspension of the treatment phase.

The CE-certified stimulators are charged with 10 stimulations at baseline, V1, V2, and V3. These stimulators are pre-programmed with either verum or sham codes that decide whether the stimulations are active or sham. The codes are randomized pre-trial into a list using an online tool by neuroCare (https://ctrandomization.cancer.gov/tool/). Each participant is assigned a code from the randomized list in order of trial enrolment date. This assignment of either a verum or sham code from the randomized list is performed by an independent researcher not otherwise involved in the study. The participants are not aware of their codes. Neither the operator nor the rater knows whether the individual stimulation ID codes are verum or placebo. As no conclusions can be made on the stimulation condition, double-blinding is ensured [41].

### Assessments

The time and events schedule (Table 1) summarizes the frequency and timing of treatment and study assessments. At screening, each participant will undergo a diagnostic interview using M.I.N.I. A clinician, who is familiar with the DSM-5 classification and diagnostic criteria will perform the interview. The M.I.N.I ensures that study participants meet the diagnostic criteria for an episode of MDD according to DSM-5. Efficacy will be assessed using the MADRS (primary outcome) at 8 timepoints. Further assessments such as the BDI, CGI-I/-S, and GAF also take place every visit. Additionally, at the baseline visit, the Edinburgh Handedness Inventory (EHI) and ATHF will be assessed. Afterwards, tDCS training will take place. During the treatment period, CRQs are turned in to the research team each visit for safety and tolerability evaluation.

**Table 1 Tab1:** Times and events schedule

**Phase**	**Pre-treatment period**		**Treatment period**																														**Follow-up period**	
**Week**	** − 1**		**1**					**2**					**3**					**4**					**5**					**6**					**10**	**14**
**Study visit**	**S**	**B**					**1**					**2**										**3**										**4**	**5**	**6**
**Day**	-14/-5	-4/1	1	2	3	4	5					12					19					26					33					40	68	96
**Screening, treatment, and administrative procedures**																																		
Informed consent^a^	**√**																																	
Medical and psychiatric (family) history, demographic data	**√**																																	
M.I.N.I	**√**																																	
HDRS-17	**√**																																	
Pregnancy test		**√**																																
Concomitant treatment^b^		**√**																														**√**		
EHI-8, ATHF		**√**																																
tDCS training		**√**																																
Blinding check																																**√**		
**Efficacy measures**																																		
MADRS	**√**	**√**					**√**					**√**										**√**										**√**	**√**	**√**
BDI-II, CGI, GAF,		**√**					**√**					**√**										**√**										**√**	**√**	**√**
**Safety measures**																																		
CRQ			**√**	**√**	**√**	**√**	**√**	**√**	**√**	**√**	**√**	**√**	**√**	**√**	**√**	**√**	**√**	**√**	**√**	**√**	**√**	**√**	**√**	**√**	**√**	**√**	**√**	**√**	**√**	**√**	**√**	**√**		
**Adjunctive investigations**^e^																																		
fMRI, sMRI, E-field Modelling		**√**																																

^a^Informed consent has to be obtained prior to any study-related procedure

^b^Medication, but also the kind of psychotherapeutic intervention (e.g., group therapy or individual therapy), duration, and frequency have to be recorded

Assessments during visit 4 (week 6, post-intervention) are crucial in case of premature discontinuation of the study. Participants will drop out of the study if there is attempted suicide or presentation of suicidal ideation (based on a score of 4 or higher in MADRS item 10).

### Magnetic resonance imaging (MRI)

A total of 20 participants can be offered optional cMRI, comprising of sMRI and fMRI scans, as two simultaneous additional baseline examinations prior to stimulation start. The sMRI scan would be performed for anatomical measurements and E-field modeling, whereas fMRI resting state scans, conducted at the same time, would supplementarily measure brain baseline activity through changes in the blood-oxgen-level-dependent signal (BOLD). The entire MRI protocol is expected to be approximately 30 min in length. Measurements will be performed on a Siemens Prisma 3 T MR scanner (3-T MAGNETOM Prisma, Siemens Healthineers, Erlangen, Germany) at the LMU Department of Psychiatry and Psychotherapy.

### Electric field modeling

Based on structural MRI measurements, models of tDCS-induced E-fields will be computed using SimNIBS 3.2.2., an open-source program (www.simnibs.de) [51, 52]. The intensity and shape of the E-field over the target region, the prefrontal cortex, are calculated from the anatomical scans of each respective participant. The characteristics of the E-field depend on, for example, the amount of cerebrospinal fluid and the distance between the electrode and the cortex. The different distribution of the E-fields could also explain interindividual differences in participants’ response patterns to tDCS.

### Safety and adverse events monitoring

The risk of (severe) adverse events or even health damage associated with prefrontal tDCS is expected to be minimal. Common adverse effects are generally mild [7]: skin irritation (22%), local sensations on the skin (40%), mild headaches (14%), and drowsiness (29%). After each treatment, participants complete a CRQ to record any adverse effects. These CRQS are monitored every study visit by the research team. A member of the study team will be available for any concerns until 8 pm via a study cellphone. For problems outside office hours, participants will be instructed to come to the psychiatric emergency department of the university hospital. Participants will be withdrawn from the study if there is any risk for suicidality (based on a score of 4 or more in MADRS item 10). Further reasons for withdrawal are pregnancy and SAE occurrence. If the investigators conclude that it is best for a participant to stop treatment for safety reasons, e.g., after an AE, the participant will be withdrawn from the trial. In these cases, unblinding is done by a scientist, who is not involved in the trial.

### Data management plan and statistics

The data will be collected and processed with appropriate precautions to ensure confidentiality and abide by data protection laws and regulations. Participants will be informed that all data will be appropriately pseudonymized and that this data may be used for analysis and publication purposes. Data analysis will be conducted using R software and IBM SPSS Statistics. Safety will be evaluated exploratively based on drop-out rates, technical parameters, and AEs. To evaluate the intervention’s feasibility, we will determine the mean number of sessions that were missed by participants. A 95% confidence interval will be computed around this mean to account for potential variability in this measure. Our predefined feasibility criterion for the intervention is met if, within the study, at least 75% of the participants fully complete 20 out of the 30 intervention sessions. To analyze the efficacy of the tDCS intervention, analysis of covariance (ANCOVA) will be used. The change in outcome (MADRS, BDI, CGI, and GAF) will form the dependent variable, treatment allocation (active vs. sham), and the fixed effect, and the baseline level of outcome will be entered as a covariate to control for baseline differences. This will reduce residual variability, increase the precision of the estimate, and address regression to the mean. The treatment effect will be reported with 95% confidence intervals.

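### Withdrawal from the study is triggered by an item of the MADRS itself, and a single-time-point ANCOVA then leaves the secondary week-6 MADRS comparison at risk of bias, most likely toward no difference

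*Protocol article*

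**What the plan says.** **Withdrawal.** The section on safety and adverse events monitoring has participants "withdrawn from the study if there is any risk for suicidality (based on a score of 4 or more in MADRS item 10"). The notes under Table 1 repeat the rule: "Participants will drop out of the study if there is attempted suicide or presentation of suicidal ideation", again at an item 10 score of 4 or higher. The safety section adds: "Further reasons for withdrawal are pregnancy and SAE occurrence". It also says that a participant whose treatment the investigators stop for safety reasons is withdrawn from the trial. Stopping stimulation and leaving the study are written as one event.

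**Entry.** The exclusion criteria rule out the same score: "Acute risk for suicide, defined as a score of 4–10 on item 10 of the MADRS".

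**Early discontinuation.** The notes under Table 1 say: "Assessments during visit 4 (week 6, post-intervention) are crucial in case of premature discontinuation of the study". They do not say whether this rating is brought forward to the day of stopping or taken at calendar week 6.

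**Analysis.** The statistics section states: "To analyze the efficacy of the tDCS intervention, analysis of covariance (ANCOVA) will be used". The dependent variable is the change in the outcome, allocation is the fixed effect, and "the baseline level of outcome will be entered as a covariate to control for baseline differences". The study objectives set the effectiveness time point at 6 weeks. Table 1 also schedules the MADRS at visits 1, 2 and 3 (days 5, 12 and 26), but the stated model gives these ratings no role.

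**Status of the outcome.** Abstract and study objectives make feasibility primary and effectiveness secondary. The Assessments section labels the MADRS primary; this note treats it as secondary.

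**The concern.** Because an item 10 score of 4 or more is excluded at entry, anyone who later reaches it has worsened on part of the outcome measure. Whether a week-6 score exists then depends on how the participant was doing. The safety withdrawals may add to this.

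If those participants are left out, each arm is represented by the people who did well enough to stay. If an early score stands in for week 6, their course after stopping is not seen. In either case the treatment difference shifts when the two arms lose different numbers of such participants, or lose participants with different prognoses. If tDCS works, sham would be expected to lose more, and the difference would shrink.

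The groups are small (the abstract gives 32 participants, the Methods 40, so 16 to 20 per arm), and a few withdrawals count. An analysis plan can choose a model later, but it cannot restore week-6 or follow-up ratings that were never taken because the participant had left the study.

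**Working it through.** **1. The plan's own figure.** Inputs from the sample size section: difference in change 12.58, SD of change 11.01, two-sided alpha 0.05, power 0.90. Then d = 12.58/11.01 = 1.14. The noncentral t gives power 0.898 at 17 per group and 0.915 at 18, so 18 per group and 36 in total; 36/0.90 = 40. The stated figures reproduce. Drop-out enters only here, as a 10% inflation.

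**2. Bias of a completers' analysis.** Let p be the share withdrawn in an arm, and g the amount by which the withdrawn participants' unseen week-6 change is worse than that of completers. The full-arm mean equals the completers' mean plus p × g, so

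shift toward zero = p(sham) × g(sham) − p(active) × g(active).

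The documents give neither p by arm nor g. Assume 20 per arm and the same g in both arms, at about 0.5, 1 and 1.5 SD:

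| Withdrawn, sham / active | g = 5.5 | g = 11.01 | g = 16.5 |
|---|---|---|---|
| 2 / 0 | 0.55 | 1.10 | 1.65 |
| 4 / 0 | 1.10 | 2.20 | 3.30 |
| 2 / 2 | 0 | 0 | 0 |
| 0 / 2 | −0.55 | −1.10 | −1.65 |

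Example: 4/20 × 16.5 = 3.30, which is 26% of 12.58. Four is the whole planned drop-out (10% of 40). A negative sign means that the effect is inflated. With 16 sham and 20 active participants left and SD 11.01, power is 0.911 without bias and 0.685 with a shift of 3.3.

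**3. One item-based rule acting alike in both arms.** Large-sample simulation, 300,000 per arm. Assumptions: baseline mean 28 (SD 4), sham mean change −8, SD of change about 11.01. An item score is linked to the concurrent MADRS total with weight 0.4, 0.7 or 0.9, and a participant is withdrawn at the first of weeks 1, 2 or 4 at which the item passes a threshold. True effect 12.58:

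| Weight | Withdrawn, sham / active | Completers' shift toward zero | Last rating carried in |
|---|---|---|---|
| 0.4 | 11% / 7% | 0.14 | 0.44 |
| 0.4 | 23% / 17% | 0.25 | 1.13 |
| 0.7 | 5% / 2% | 0.25 | 0.05 |
| 0.7 | 14% / 7% | 0.52 | 0.30 |
| 0.9 | 2% / 1% | 0.22 | −0.04 |
| 0.9 | 8% / 3% | 0.55 | −0.06 |
| 0.9 | 20% / 9% | 1.10 | 0.13 |

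For sham withdrawal of 2% to 20%, the completers' shift is about 0.1 to 1.1 points; with a true effect of 6 it is about 0.1 to 0.65. With no true effect both methods are off by about zero. In the rows with 2% to 20% sham withdrawal, the simulated gap g in sham ran from 2.9 to 9.9 points. The 16.5 in step 2 is therefore an outer case.

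**4. Cost in precision of using all visits.** A second simulation (N = 40, 4,000 trials per setting) withdrew participants after a total-score worsening of more than 6 points, about 15% of sham and 5% to 9% of active. The SD of the estimate was 3.68 for a likelihood analysis of all visits against 3.44 for completers at a true effect of 6, and 3.67 against 3.49 at 12.58. The ratios are 1.07 and 1.05, so the SE is 5% to 7% larger. Mean estimates were 5.97 against 5.12, and 12.57 against 11.16.

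**The case against.** The strongest reply is that the article names a model but no analysis set and no rule for withdrawn participants, and that a condensed article commonly leaves both to the analysis plan. That stands. A reader might infer that withdrawn participants are dropped from the ANCOVA, and the text does not say so. The note on visit 4 points, if anything, to a rating when someone stops. That would capture the bad score, and in step 3 the resulting error is mostly small.

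A reader might also take the second simulation as showing an 11% to 15% attenuation (11.16 for 12.58; 5.12 for 6). The documents do not support that as a headline. It uses a total-score rule, not the item 10 rule; its arm rates are assumed; and withdrawal on an observed score is missing at random by construction, which favours a likelihood model. Its own figures do not clearly favour that model on overall accuracy. Root mean squared error at a true effect of 6 is √(0.88² + 3.44²) = 3.55 for completers against 3.68; at 12.58 it is √(1.42² + 3.49²) = 3.77 against 3.67.

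Baseline-adjusted ANCOVA is an accepted analysis, and this is a secondary outcome in a pilot. Asking for ratings after withdrawal is also more than a change of analysis wording.

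The reply does not remove two facts. As written, withdrawal ends study participation on worsening in the outcome scale, and ratings not taken cannot be supplied by a later plan.

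**Conclusion.** The concern holds as a risk of bias in the secondary week-6 MADRS comparison. The most likely direction is toward no difference, if sham participants withdraw more often; more withdrawals on active could inflate the effect.

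The size depends on withdrawal counts by arm that the documents do not give. Under the assumptions above, and against a difference of 12.58 points, it is:

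- about 0.1 to 1.1 points for a completers' analysis when one item-based rule acts in both arms;
- up to about 3.3 points if all four planned drop-outs were sham participants with poor outcomes;
- about 0 to 0.4 points if the last rating is carried in, and 1.1 at 23% sham withdrawal.

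The stronger statement, that the comparison is biased, does not follow. With no treatment effect, or with balanced withdrawals and equal gaps, the bias is about zero, so the rule produces no systematic false positive. The sample size calculation and the primary feasibility criterion are not affected. The change is still worth making, because it is cheap and part of it must be settled before data are lost.

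**What to change.** Leave the clinical stopping rules unchanged. Then:

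1. Record stimulation stopped and study follow-up ended as two separate events.
2. Seek the scheduled MADRS at day 40, and at days 68 and 96, from participants who stopped stimulation and agree to be rated.
3. State when the visit 4 assessment is done after premature discontinuation. Enter an early rating at the visit when it was taken, not as week 6.
4. Estimate the week-6 effect in all randomised participants as allocated, with a repeated-measures model of MADRS change at visits 1 to 4: treatment, visit, treatment-by-visit and baseline MADRS. Use small-sample degrees of freedom and keep the model simple, given 16 to 20 per arm.
5. Keep the planned ANCOVA as a sensitivity analysis. Add one that assigns poor outcomes to participants withdrawn on item 10, since the model in step 4 assumes that missingness is explained by the observed ratings.

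The cost is some protocol and analysis wording, a few extra retained ratings, and an SE about 5% to 7% larger than for completers in the simulation above.
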